## Abstract

**Background:**

Many studies were conducted to assess the benefit/risk ratio of EMONO (Equimolar Mixture of Oxygen and Nitrous Oxide) in France before it was authorized for use outside the hospital setting in 2009. The main objective of this project is to evaluate the effects sought and felt by children when EMONO is used in paediatric dentistry. The secondary objectives are to (i) evaluate the appreciation of EMONO by the children, (ii) characterize children who experience both analgesia and anxiolysis, (iii) evaluate children’s appetite for EMONO and characterize children with a high appetite and (iv) evaluate the impact of the difference in practice among the French dental service university hospitals on anxiety. The maintenance of a framework for the safe use of this drug, whose place in dental care is fundamental, is essential. Twelve of the 16 French dental service university hospitals agreed to participate in this study.

**Methods:**

MEOPAeDent is an observational, descriptive, transversal study that aims to evaluate the effects sought and felt by children when EMONO is used in paediatric dentistry. Subjects requiring dental care under EMONO are recruited by 12 French dental service university hospitals. Patients aged from 3 to 15 years are recruited for the study when they visit a dental service of a French university hospital requiring dental care under EMONO. The investigator collects the necessary data from the child’s medical records, from his own observations and from questions posed to the child and his/her parents. A survey is completed at the first and final sessions of dental care under EMONO.

**Discussion:**

This study will provide an evaluation of the effects of EMONO on the French paediatric population in need of dental care as well as evaluate the appetite for the use of this substance. The results will first be used to provide additional data that is essential to monitor the use of a product with an authorization to use it outside of hospitals from 2009 in France, confirm its safety for use and justify its framework of application.

**Trial registration:**

ClinicalTrials.gov ID: NCT03453411 registered 2 March 2018.

## Background

EMONO is an equimolar mixture of oxygen and nitrous oxide available in France for dental care. It has an analgesic effect with a reduction of the perception threshold of different painful stimuli and an anxiolytic effect. It causes modifications in consciousness: patients are relaxed, sedated and less aware of their surroundings. Pulmonary absorption and elimination of nitrous oxide occur very quickly because of its low solubility in blood and tissues, explaining the rapidity of the analgesic effect and quick return to the initial status after discontinuation of inhalation [1–5].

Based on the product characteristics summary available in the French government’s public drug database [base-donnees-publique.medicaments.gouv.fr/], EMONO indications in dentistry are dental care for infants, children and adolescents, as well as for anxious and patients with disabilities. Administered in combination with oxygen, it improves the cooperation of patients during anxiety-related or painful medical and paramedical procedures (mild to moderate pain) and offers a short duration per use. EMONO in dental care provides great benefit to patients with behavioural disorders, mental retardation or excessive anxiety. Patient cooperation tends to improve under EMONO and, when not used in conjunction with psychotropic agents [6–8], the use of EMONO is safe.

In France, ANSM (French National Agency for Medicines and Health Products Safety) has classified EMONO as a drug known to produce dependency. EMONO obtained its approval in 2001 in France in several indications, particularly in dental care, in hospitals exclusively, for children and patients with anxiety or disability. Its use was considered as very safe in this context [9, 10]. In 2009, the authorization to use it outside the hospital setting has led to a risk management plan implementation. The Nantes CEIP-A (Centers for the Evaluation of and Information on Drug Dependence) has been entrusted with EMONO supervision. It was shown that nitrous oxide could cause problematic consumption: 31 cases of problematic consumption of nitrous oxide alone or in a mixture with oxygen were reported over a period from 1978 to 2014 [11–37]. Classical vulnerability factors of addiction have been reported (family context, psychiatric vulnerability). Several problematic consumer groups with different characteristics have been defined: the first group includes users taking pure nitrous oxide for recreational purposes, the second group is characterized as nitrous oxide users taking it for medical purposes, and the third group is characterized as those taking it in the presence of health professionals, mainly dentists using the nitrous oxide/oxygen mixture [11–37]. However, none of the patients in the ANSM reports were described as those with dependence or abuse due to EMONO use in dental care. The desired effects in patients during EMONO use are relative anxiolysis and analgesia with a preserved state of awakening [2].

The dental service of university hospitals often represent one of the last resorts for dental care at the regional level for patients with limited cooperation because of their disabilities or anxiety. The use of EMONO is often implemented several times for each patient. Indeed, very few dentists nearby use EMONO, leading to a large influx of patients at the university hospital service. However, the authorization to use it outside the hospital setting will lead to an increasing number of dentists using EMONO.

EMONO in paediatric dental care is particularly useful in which EMONO can be administered as the first psychoactive substance known for its positive effects (euphoria). Health professionals observe children who take EMONO daily. The main objective of this project is to evaluate the effects sought and felt by children when EMONO is used in paediatric dentistry. The secondary objectives are to (i) evaluate the appreciation of EMONO by a child, (ii) characterize children who experience both analgesia and anxiolysis, (iii) evaluate children’s appetite for EMONO and characterize children with high appetite and (iv) evaluate the impact of various product applications among the French dental service university hospitals on anxiety. The maintenance of the framework for the safe use of this drug, which is placed in dental care as fundamental, and the benefit ratio as very favourable, is essential. Twelve French dental service university hospitals have agreed to set up this study.

## Methods

### Study design

This observational, descriptive, transversal study aims to evaluate the effects sought and felt by children when EMONO is used in paediatric dentistry. Subjects needing dental care under EMONO were recruited by 12 French dental service university hospitals. Thereafter, the data are collected by practitioner observation, direct interview after dental care under EMONO and using the subject’s medical record.

This project received the financial support from the French National Agency for Medicines and Health Products Safety (ANSM) as part of the 2017 ‘national call for tender’ and also received funding from the local Scientific Committee of the Faculty of Dental Surgery in Nantes as part of the 2017 call for tender.

### Setting of the study

The Dental Service of Nantes University Hospital, along with the Nantes CEIP-A, is the coordinating investigation centre in charge of the general management, monitoring and coordinating of the project. A consortium was set up with partner dental service university hospitals in charge of coordinating the project at the local level in their research area (dental service university hospitals in Brest, Bordeaux, Toulouse, Lyon, Paris Descartes, Nancy, Lille, Reims, Nice, Marseille and Strasbourg). The dental service university hospitals participating in the study are spread over the metropolitan territories of France. The period of inclusion for each participating dental service university hospital is 12 months, and there is no follow up after the patient’s assessment and his/her final care session.

For this national multicentric study, a multi-disciplinary steering committee, comprising pharmacologists, dentists, psychiatrists, methodologists, biostatisticians and clinical research staff, was set up to draft the study protocol. Its mission is to ensure the study’s validity in terms of the scientific content and methodology. The leading committee will handle any practical problems occurring during the study and where appropriate, decide on amendments to the protocol. The committee shall meet regularly, and whenever necessary, to approve aspects concerning practical organization and to answer any questions raised during the study.

### Participants

#### Eligibility criteria

The patients are recruited for the study by their dentist when they visit the dental service university hospitals for their dental care under EMONO, according to the following inclusion criteria:Children aged 3 to 15 yearsRequiring dental care under EMONOBeing able to provide the details to answer the questionnaire of the studyCooperating along with his/her parents and ready to participate in the study

The exclusion criteria of the study are as follows:

Patients are restricted from participation if their dental care can be performed in a vigilant state or involves several important treatments, justifying general anaesthesia. Finally, children who cannot understand the questionnaire will not be allowed to participate.

### Patient recruitment

Each dentist from a dental service university hospital participating in the study recruits patients needing dental care under EMONO over a 12-month period. If the patient meets all the inclusion criteria, the dentist asks the child and his or her parents or legal guardian, if he or she wishes to participate in the study, providing clear and appropriate verbal and written information on the study (objectives, scientific interest, and practical procedures).

Without any delay, the dentist collects the patient’s oral consent (as well as that from at least one of the parents or legal guardians). The lack of delay is due to the design of the study, which has been approved by the Committee for the Protection of Persons (CPP).

### Consent for participation

At inclusion, the patients receive an information leaflet for their age range, as well as their parents or legal guardian. The investigator will note in the patient’s file that the patient and parents have been orally informed, received the briefing note and gave their oral consent to participate in the research. At least one parent of all children, regardless of the age of the child, must be informed and must consent.

### Ethics statement

This non-interventional study has been declared to the French Data Protection Body (CNIL) and received a favourable opinion from the Committee for the Protection of Persons. It has also been registered at ClinicalTrials.gov.

### Variables and data measurement

Data for the analysis are collected in two steps, through the survey completed by the dentist at both the first and final sessions of dental care under EMONO. If the patient requires only one treatment session, only the first part of the questionnaire is completed.

### Survey

Once the investigator receives oral consent to participate in the research from the patients and at least one of the parents (or legal guardian), the necessary data are collected from the child’s medical records, from his own observations and from questions to the child and his/her parents. A survey is completed at both the first and final sessions of dental care under EMONO.

#### Primary endpoint

Our primary endpoint, to describe the effects of EMONO that are felt and sought during care during the first and last treatment sessions, will be performed by questioning the patients comprehensively about the presence or absence of each expected effect of EMONO (waking state preserved, no abolition of judgment, relative analgesia, anxiolysis), and each adverse event (slight decrease in consciousness, agitation, anxiety, euphoric effect, nausea or vomiting, sensation distortion) at the first and last treatment sessions. The presence of unexpected “other” effects will also be indicated. When scored as present, all effects will be considered as experienced by the patient.

For each effect felt, the patient will be asked about his or her perception of the effect (positive or not).

To describe the effects felt and sought with EMONO use, the prevalence of each effect felt will be calculated, and the proportion of patients who felt this effect and found it pleasant (positive) will also be indicated.

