#### Secondary endpoints

*Three parameters will be used to evaluate the child’s assessment of EMONO during the first session of care:*
VAS (Visual analogue scale): the patient marks on the line the point he/she feel represents their perception and eventually their appreciation of contact with EMONOChoice of the child with an adapted drug-liking test: the patient will be asked if he/she prefers to exchange the toy that he/she traditionally receives at the end of the care against an EMONO inhalation without care [38, 39]The child’s will to continue care in the case of adverse effects

*Three parameters will define children who experience both analgesia and anxiolysis during the first session of care:*
Decreased score on the anxiety scale (Venham modified by Veerkamp) before and after inhalation of EMONOPresence of anxiolysis among the effects feltPresence of analgesia among the effects felt

We will estimate the prevalence of children for whom at least one of the first two parameters and the third parameter are present during the same session of EMONO use.

*The parameter “Presence of signs that the child is trying to prolong contact with EMONO” will be used to define patients with a higher appetite for EMONO (shown by patients’ attempt to extend the duration of EMONO use physically or verbally) during the first session of care. The following three parameters will characterize these children:*
Table answering the questions about the presence of expected effects of EMONO and their perceptionsMedical historyFamily situation of parents and anxiety of parents [40–42]

*Three parameters will make it possible to evaluate the impact of the difference of practice between the French dental service university hospitals regarding the anxiety during the first and last sessions of care:*
Decreased score on the anxiety scale (Venham modified by Veerkamp) before and after inhalation of EMONOUse of a sedative premedicationPatient management using closed boxes or open spaces

The different practices evaluated in the French dental service university hospital will include the use or absence of a sedative premedication and management of the patient in closed or open boxes.

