### Statistical methods

All the evaluation parameters will be subjected to a descriptive analysis. The quantitative variable evaluation parameters will be described using position parameters (mean or median) and dispersion (standard deviation, interquartile range and range). Normality of their distribution will be assessed (normality test and evaluation using the relevant graphic tools). The qualitative variable evaluation parameters will be shown in the form of number and frequency tables for each modality.

To answer the main objective (description of the effects felt and sought using EMONO), the prevalence of each effect felt will be calculated, and the proportion of patients who felt this effect and found it pleasant (positive) will also be indicated.

Each criterion to evaluate the EMONO’s assessment by the child will be analysed independently (average for the VAS score, prevalence of drug-liking and continuation of care).

The prevalence of children who experience both analgesia and anxiolysis will be estimated. A multivariate logistic regression model will be applied to define the associated factors: child/parent socio-demographic characteristics and antecedents.

The prevalence of children with a higher appetite for EMONO will be estimated. A multivariate logistic regression model will be applied to define the associated factors: socio-demographic child/parent characteristics, medical history, presence of expected EMONO effects and their perceptions.

The impact of care practices (sedative premedication and closed/open box management) on anxiety will be evaluated using average comparisons (Student’s tests) of the anxiety score before and after the inhalation of EMONO. A comparison will also be made on the difference in the pre- and post-inhalation score.

The evolution of EMONO intake between the first and last sessions will be described in terms of the prevalence (amnesic effect, tolerance, concern), appetite difference and difference between the effective dosage at the first and last treatment sessions will be calculated.

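### Anxiety and agitation count as adverse events of EMONO whenever present, with no reference to the child's state before inhalation, so pre-existing anxiety can be reported as an adverse event

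*Protocol article*

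**What the plan says.** The protocol article, under *Primary endpoint*, states the aim as "to describe the effects of EMONO that are felt and sought during care during the first and last treatment sessions". Children are asked about the presence or absence of each expected effect, anxiolysis among them, and of "each adverse event (slight decrease in consciousness, agitation, anxiety, euphoric effect, nausea or vomiting, sensation distortion) at the first and last treatment sessions". The counting rule follows: "When scored as present, all effects will be considered as experienced by the patient". For each effect felt, the child is also asked whether it was perceived as positive.

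Under *Statistical methods* the primary analysis is purely descriptive, giving for each effect how often it was felt and how often it was liked: "the prevalence of each effect felt will be calculated, and the proportion of patients who felt this effect and found it pleasant (positive) will also".

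On the population, *Background* says "EMONO indications in dentistry are dental care for infants, children and adolescents, as well as for anxious and patients with disabilities". It describes the university services as a regional last resort for patients whose cooperation is limited by disability or anxiety. *Eligibility criteria* exclude children who could be treated in a vigilant state.

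An anxiety measure from before inhalation exists. *Secondary endpoints* lists "Decreased score on the anxiety scale (Venham modified by Veerkamp) before and after inhalation" of EMONO, once for the combined analgesia and anxiolysis definition (first session) and once for the comparison of care practices (first and last sessions).

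**The concern.** Most items on the adverse-event list, such as nausea or a euphoric effect, would seldom be present before the mask is applied. Anxiety and agitation are different: the children are selected in part because they are anxious or cooperate poorly. A rule that counts the state without asking about change cannot tell anxiety that EMONO failed to relieve from anxiety that appeared or grew under EMONO. The first is absence of benefit, the second a possible harm.

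The list is also uneven. Anxiolysis is by nature a change from before, while anxiety is scored as a state.

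These prevalences are primary results. The *Discussion* says the therapeutic and non-therapeutic effects are evaluated in order to estimate the benefit/risk ratio, and that the study is expected to confirm safety of use. One secondary parameter, the child's willingness to continue care when adverse effects occur, also depends on who is classed as having had one.

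**Working it through.** No figure in the article turns on this point, so there is none to reproduce. The check has three parts.

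**1. The counting rule applied to four kinds of child**

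| Before inhalation | Under or after EMONO | Counted as anxiolysis | Counted as adverse event (anxiety) |
|---|---|---|---|
| Anxious | Unchanged | No | Yes |
| Anxious | Less anxious, not calm | Yes | Can be yes |
| Anxious | More anxious | No | Yes |
| Calm | Anxious | No | Yes |

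Rows 1, 3 and 4 give the same result, although only rows 3 and 4 are new or worse. Row 2 can enter the benefit count and the adverse-event count together.

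**2. Whether the plan elsewhere supplies the missing reference**

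The score before and after inhalation is assigned only to the two secondary endpoints named above. *Statistical methods* uses it for Student's tests between care practices, on the scores and on their difference. Neither the primary endpoint nor its analysis refers to it. For agitation, no pre-inhalation measure is described.

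**3. What can be said about size**

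Input from the documents: 62% of pilot patients had an anxiolytic effect (*Discussion*), so 100% − 62% = 38% had none. The recruitment aim is 1300 (*Study size*).

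Input not in the documents: the share *b* of children anxious before inhalation. It is varied from 30% to 90% as an assumption.

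Illustration: suppose the gas causes no anxiety, the 62% applies equally to children anxious beforehand, and those not relieved stay anxious. The prevalence of anxiety as an adverse event is then *b* × 0.38, all of it pre-existing.

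If the equal-rate assumption is dropped and only the two margins (*b* and 38%) are kept, the share both anxious beforehand and without anxiolysis lies between max(0, *b* + 0.38 − 1) and min(*b*, 0.38).

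| *b* (assumed) | *b* × 0.38 | Children of 1300 | Limits from the margins alone |
|---|---|---|---|
| 30% | 11.4% | 148 | 0% to 30% |
| 50% | 19.0% | 247 | 0% to 38% |
| 70% | 26.6% | 346 | 8% to 38% |
| 90% | 34.2% | 445 | 28% to 38% |

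The ranges are too wide to serve as estimates. The 38% is a ceiling only for children without anxiolysis. It includes children who were never anxious and had nothing to relieve, and it leaves out partly relieved children, who could add to the anxiety count.

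**The case against.** The best defence is that the article condenses a fuller protocol and the questionnaire is not shown. The item concerns felt effects of a product and is put in an interview adapted to age and comprehension. It may be worded so that the child attributes the anxiety to the gas. The counting sentence could then be no more than a scoring convention. This has some force and cannot be excluded. But the article itself describes a question about presence or absence, states no attribution step, and puts it to respondents aged 3 to 15. The rule as written admits any anxiety that is present.

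A second objection concerns the remedy. The endpoint is what children feel, and a scale score should not overrule their answer. Inhalation also coincides with dental care, so a higher score afterwards may reflect the procedure, and a before/after pair can miss brief anxiety in between. All of this stands. It argues for reporting the child's answer alongside the score and against replacing it.

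Three stronger readings are tempting, and the documents do not support them:

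- **That baseline anxiety will be reported as toxicity of the gas.** The article speaks of adverse events and effects, never of toxicity, and not every child is anxious beforehand.
- **That the flaw distorts a comparison between hospitals.** No comparison of these prevalences between hospitals is planned, and the comparison of practices already uses scores before and after inhalation.
- **That the true rate is overstated by some multiple.** This needs a rate of new or worse anxiety, which the article does not give. Adding such a rate to the 38% would also count children twice, because a child whose anxiety is new or worse should already be among those without anxiolysis.

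**Conclusion.** The point holds in a limited form. As written, the primary endpoint can count pre-existing, unrelieved anxiety or agitation as an adverse event of EMONO, and can count a partly relieved child on both sides of the benefit/risk balance. This follows from the text alone, subject to the wording of a questionnaire that is not shown.

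Its size is unknown. The only documented anchor is the pilot's 38% without anxiolysis, which limits wholly unrelieved anxiety if the pilot rate carries over to the national sample. The 11% to 34% in the working is an illustration that rests on an assumed share of anxious children and an assumed equal rate of relief.

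The defect lies in definition and labelling. It does not invalidate the study, and for anxiety the data needed to deal with it are already being collected. It should be settled before these two prevalences are used in a benefit/risk statement.

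**What to change.** **Anxiety.** Keep the child-reported item unchanged. At the first and last sessions, report its prevalence by pre-inhalation Venham-Veerkamp score and by change in score (higher, unchanged, lower). Use the term adverse event only where the anxiety is new or worse than before inhalation, and label the remainder *present during care / not relieved*. The rows for children with the lowest scores beforehand show where reported anxiety is unlikely to have been carried over.

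**Agitation.** Add one pre-inhalation item and report it in the same way. If the form can no longer be changed, label the prevalence *present during care*.

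**Crude figures.** Show the unadjusted prevalence of both symptoms beside these tables, and state that a rise in score does not separate the gas from the dental procedure and that a score taken after inhalation may miss transient anxiety.

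**Cost.** A few more tables from scores already taken at both sessions, and one added tick-box for agitation. There is no effect on sample size or recruitment.
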